### Data Collection

Data for primary and some secondary outcome measures will be collected from the LeoMed platform until POD 30, with the exception of same-day cancellations. These data will be collected on POD 1 from the electronic medical record (EMR) system by 1 member of the research team (Table 1). In the absence of spontaneous responses from patients at POD 30 or if the forms are incomplete, patients will be called by one of the research assistants to assess the indicators included in the cost-effectiveness and cost-utility analyses. If a postoperative event is reported via the form, the patient will also be contacted personally by telephone.

For each patient, data will be systematically registered and archived on a local secure server. Patients will be identified using a unique numeric code, and all patient data will be anonymized to ensure confidentiality. All data will be extracted and cross-referenced with Oacis (Telus Health), the EMR system used at CHUM.

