## Introduction

Outpatient surgeries have increased significantly in the last 3 decades [1]. In Canada, there was an overall 30% increase in outpatient surgeries between the fiscal years 1995-1996 and 2005-2006 [2]. In some countries, day surgeries account for more than 70% of all elective procedures [3]. Nowadays, it is common to perform day surgeries for both higher-risk patients and procedures [4]. However, postoperative measures currently in place to support and follow patients undergoing day surgeries are suboptimal. Indeed, a recent Canadian study has shown that the same-day cancellation rate for outpatient surgeries ranges from 8% to 10% [5,6]. The authors of that study also mentioned that 60% of these cancellations could have been avoided with better preoperative support [7]. Despite current recommendations, adverse postoperative events are very rarely searched for or detected by health care institutions [8-10]. The most common reasons for readmission, emergency department consultation, or unplanned medical visits are postoperative pain, nausea, and vomiting [10]. In addition, the prevalence of moderate-to-severe postoperative pain after ambulatory surgery ranges from 21% to 30% at 24 hours, and as much as 24% to 43% at 7 days [11,12]. This could lead to inappropriate postoperative use of opioids [13]. Inadequate pain relief is also one of the main risk factors for impairment of patients’ overall quality of life after surgery [14]. A recent report by the Canadian Institute for Health Information showed that patients scheduled for day surgery in Canadian teaching hospitals return to the emergency department or are readmitted within 30 days postoperatively at incidence rates of 9.4% and 7.3%, respectively [15]. The additional costs associated with these cancellations and unplanned readmissions amount to several billion dollars every year [15].

In efforts to ensure better perioperative support and follow-up for patients undergoing day surgeries, many tools have been developed [16]. With recent technological advances and with the widespread use of smartphones and tablets, digital solutions have been suggested to guide and follow these patients [17].

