### Population

All patients aged over 18 years who undergo elective day surgery under general or regional anesthesia at CHUM will be eligible. All included patients must (1) have internet access and (2) understand written and oral French or English. Patients were possibly excluded at two stages: (1) before randomization, if they were unable to learn and use the digital technologies or if they refused to participate, and (2) after randomization, in cases of conversions from outpatient to inpatient hospitalization on the day of surgery or in cases of last-minute postponement of the surgery to a later date. Figure 1 shows the trial flowchart.

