	**Assessments from the electronic medical record system**														
	Same-day cancellations							✓							
	Calls to CHUM online support													✓	

^a^POD: postoperative day.

^b^CHUM: Centre hospitalier de l’Université de Montréal.

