### Primary Outcome

The primary outcome will be the cost-effectiveness of the LeoMed telecare platform deployment assessed by its direct costs, including unanticipated cancellations on the day of surgery due to preoperative instructions not being followed, calls to the local CHUM health information line, calls to the Quebec health information line (ie, 811), visits to the emergency department, and unplanned readmissions or medical visits (to family doctors or outpatient clinics) for problems related to the procedure within the first 30 days after the procedure.

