### Data Analysis

Data analysis will be performed by a team of researchers at the École des Hautes Études Commerciales in Montreal, Quebec, using SPSS (version 28; IBM Corp). All data will be analyzed according to the intention-to-treat principle. Descriptive statistics will be reported as frequencies and proportions for categorical data and means and standard deviations for continuous variables. Demographic data for the 2 groups of patients will be compared using the Mann-Whitney *U* test (for ordinal data), the chi-square test (for nominal data), and a 2-tailed *t* test (for continuous data).

Considering the Canadian guidelines for the economic evaluation of health technologies [22], the perspective of the health care system will be privileged in this study. Specifically, 2 main types of analyses will be carried out. First, all interventions in both groups related to surgery (calls to the provincial or CHUM information lines, visits to the ambulatory unit, hospital readmissions, and visits to the emergency department) will be recorded during the study to perform the cost-effectiveness analysis. Second, a cost-utility analysis will be conducted to quality-weight each effectiveness outcome measured in QALYs. QALYs will be calculated as life with the health state under study multiplied by the utility associated with that health state. CHUM’s internal data will be used to determine the cost of health care staff and the average cost of an emergency room visit for the clientele concerned in fiscal year 2019-2020. For hospitalizations, we will use the average costs calculated according to the American diagnosis-related groups method, which was applied at CHUM in 2019-2020. Technology costs will be estimated based on license prices in effect at the time of the study and amortized on a straight-line basis over a 5-year period. All calculations will be in Canadian dollars. Last, patient satisfaction with care services will be measured in both groups at the end of the trial using Likert scales adapted from Sicotte et al [23]. This protocol follows the SPIRIT (Standard Protocol Items: Recommendation for Interventional Trials) 2013 Statement for trial protocols [24].

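### Same-day cancellation is a primary cost item, but follow-up is timed from the operation and unoperated patients are removed, so a cancelled patient's costs are dropped or left unassigned

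*Protocol article*

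**What the plan says.** Primary Outcome defines the direct costs as "including unanticipated cancellations on the day of surgery due to preoperative instructions not being followed", together with information-line calls, emergency visits, readmissions and medical visits "for problems related to the procedure within the first 30 days after the procedure".

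The timing is set in three places:
- Data Collection exempts cancellations from platform collection and adds: "These data will be collected on POD 1 from the electronic medical record (EMR) system by 1 member of the research team". Table 1 puts the tick for "Same-day cancellations" in the POD 1 column.
- Intervention Group and Control Group send the forms that collect the other indicators on POD 15 and POD 30.
- Data Collection has non-responders telephoned with reference to POD 30.

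Two sections remove patients after randomisation. Population allows exclusion "in cases of last-minute postponement of the surgery to a later date". Blinding and Allocation Concealment excludes recruited patients who are not operated on within the study time frame. Data Analysis nevertheless commits to intention to treat.

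Data Analysis lists the items to be recorded for the cost-effectiveness analysis as "calls to the provincial or CHUM information lines, visits to the ambulatory unit, hospital readmissions, and visits to the emergency department". Cancellation is not among them. For unit costs it says "CHUM’s internal data will be used to determine the cost of health care staff and the average cost of an emergency room visit", and it also names sources for hospitalisation and technology costs. It names none for a cancelled surgery.

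**The concern.** The first hypothesis in the Introduction is that the platform reduces cancellations, so the number of cancelled patients is expected to differ between arms. These are the patients for whom the stated time points fail. Someone cancelled on the day has no procedure on that date, hence no POD 1, 15 or 30 and no 30-day window, and the article offers no other origin for the cost count.

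The plan leaves two routes. If the exclusions are applied, the patient leaves the analysis and takes the cancellation cost along, although that cost is part of the primary outcome. If intention to treat is applied, the patient stays, but nothing says whether the costs after a rescheduled operation count. Removing the exclusions therefore does not settle the second question.

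At stake is the primary cost comparison. An arm that prevents cancellations sends more patients to surgery on the planned date, and their postoperative costs are counted in full. The other arm's cancelled patients may have similar costs later that are never counted.

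**Working it through.** **Inputs.** From the Introduction: same-day cancellation of 8% to 10%, 60% of cancellations avoidable, and 30-day emergency return and readmission rates of 9.4% and 7.3%. From Sample Size: 500 patients per arm. The article gives no figure for the cost of a cancellation (K) or for the mean postoperative cost of an operated patient (P), so both stay symbolic. Let pA be the cancellation rate in the arm with more cancellations and pB the rate in the other arm. P is taken as equal in both arms, to isolate the effect of the time origin.

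**Rates at the extreme.** If every avoidable cancellation were prevented:
- 8% falls to 0.4 × 8% = 3.2%, so pA − pB = 0.048, or 40 against 16 patients per 500.
- 10% falls to 0.4 × 10% = 4.0%, so pA − pB = 0.060, or 50 against 20 patients per 500.

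**Full cost.** Assume cancelled patients are operated on later at the same P. The mean cost per randomised patient in an arm with cancellation rate p is p(K + P) + (1 − p)P = P + pK. The difference, A minus B, is (pA − pB)K.

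**Booked cost, patients kept but the later operation not counted.** The mean is pK + (1 − p)P. The difference is (pA − pB)(K − P).

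**Error.** Booked minus full difference is (pA − pB)(K − P) − (pA − pB)K = −(pA − pB)P. It does not depend on K. At the rates above it is −0.048P to −0.060P.

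| K | Full difference, A − B | Booked difference, A − B |
|---|---|---|
| 0 | 0 | −0.048P to −0.060P |
| P | 0.048P to 0.060P | 0 |
| 2P | 0.096P to 0.120P | 0.048P to 0.060P |

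The error is the same in every row, while the sign of the booked difference changes with K. At K = 2P, half of the true saving disappears.

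**Booked cost, cancelled patients excluded.** With these patients removed, both arms have mean P and the difference is 0. The saving (pA − pB)K then drops out altogether.

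**Exposure bound.** If no cancelled patient is operated on within follow-up, the ratio of operated fractions is:
- 0.968 / 0.92 − 1 = 5.2%
- 0.96 / 0.90 − 1 = 6.7%

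Adding 9.4% and 7.3% as if they did not overlap gives 16.7 events per 100 operated patients. Per 100 randomised, that is 15.4 against 16.2 (8% against 3.2% cancelled) or 15.0 against 16.0 (10% against 4%), a gap of about 0.8 to 1.0 events.

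**The case against.** A reader might infer that the arm with more cancellations will simply look cheaper. The documents do not support that. Primary Outcome makes the cancellation itself a direct cost, so the booked difference is (pA − pB)(K − P). It is negative only if K is below P, and neither is given.

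A reader might also infer that cancellations cannot be captured at all, because the patient has no POD 1. That goes too far. The look-up is in the medical record, needs no operation, and can naturally be read as the day after scheduled surgery. Not every clock starts at the operation either, since the notification the day before surgery must be timed from a scheduled date. The POD 1 label alone is a minor matter of wording.

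Three further objections have weight:
- **Some cancelled patients may have a window.** The exclusion for no surgery within the study time frame implies that some patients operated on later could stay, and they would have a procedure date. Data Analysis also speaks of recording surgery-related items during the study. But Population points the other way for postponed cases, so this reading depends on which passage prevails.
- **The bound is extreme.** It uses the all-cause cancellation rate, whereas the primary outcome counts only cancellations from instructions not followed. It prevents every avoidable cancellation through a notification the day before surgery, although controls get a reminder call that day. This stands, and 5.2% to 6.7% should not be read as an expected bias.
- **An article may leave date anchors to the full protocol.** That would answer a silence. Here the article states the anchors, the exclusions, intention to treat and the cost component, and together they do not work for a cancelled patient.

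**Conclusion.** The concern holds as a fault in how the primary outcome is defined. Followed as written, a patient cancelled on the day is either removed, against intention to treat and together with a primary cost item, or kept without a defined window and without the costs of the later operation.

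If cancelled patients are later operated on at similar postoperative cost, and that cost is not counted, the arm with more cancellations has its cost understated relative to the other by about (pA − pB)P, whatever a cancellation costs. This would mask part of any saving from avoided cancellations. With the article's rates and all avoidable cancellations prevented, the amount is 0.048P to 0.060P per randomised patient. The corresponding exposure excess of 5.2% to 6.7% in the intervention arm is an upper bound, which also requires that no cancelled patient is operated on within follow-up.

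The direction of the net cost difference cannot be determined, and no monetary size can be given, because K and P are not stated. The point should be corrected because it touches the primary outcome and the repair is small.

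**What to change.** Four changes to Primary Outcome, Data Collection, Table 1 and Data Analysis, with the exclusion wording brought into line:

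1. Record cancellations on the day after the first scheduled surgery date instead of POD 1.
2. Keep cancelled and rescheduled patients in their randomised arm, and reconcile the post-randomisation exclusions in Population and in Blinding and Allocation Concealment with intention to treat.
3. Count costs from the first scheduled date through 30 days after the actual operation, or through 30 days after the scheduled date if no operation takes place.
4. Add the cost of the cancellation itself to the cost items in Data Analysis, with its source.

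The price is somewhat longer follow-up for the few rescheduled patients, and follow-up of unequal length between them and the rest. Reporting the number rescheduled and their follow-up time by arm would let readers judge that. The changes are to definitions and do not alter the sample size.

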### Data Analysis

Data analysis will be performed by a team of researchers at the École des Hautes Études Commerciales in Montreal, Quebec, using SPSS (version 28; IBM Corp). All data will be analyzed according to the intention-to-treat principle. Descriptive statistics will be reported as frequencies and proportions for categorical data and means and standard deviations for continuous variables. Demographic data for the 2 groups of patients will be compared using the Mann-Whitney *U* test (for ordinal data), the chi-square test (for nominal data), and a 2-tailed *t* test (for continuous data).

Considering the Canadian guidelines for the economic evaluation of health technologies [22], the perspective of the health care system will be privileged in this study. Specifically, 2 main types of analyses will be carried out. First, all interventions in both groups related to surgery (calls to the provincial or CHUM information lines, visits to the ambulatory unit, hospital readmissions, and visits to the emergency department) will be recorded during the study to perform the cost-effectiveness analysis. Second, a cost-utility analysis will be conducted to quality-weight each effectiveness outcome measured in QALYs. QALYs will be calculated as life with the health state under study multiplied by the utility associated with that health state. CHUM’s internal data will be used to determine the cost of health care staff and the average cost of an emergency room visit for the clientele concerned in fiscal year 2019-2020. For hospitalizations, we will use the average costs calculated according to the American diagnosis-related groups method, which was applied at CHUM in 2019-2020. Technology costs will be estimated based on license prices in effect at the time of the study and amortized on a straight-line basis over a 5-year period. All calculations will be in Canadian dollars. Last, patient satisfaction with care services will be measured in both groups at the end of the trial using Likert scales adapted from Sicotte et al [23]. This protocol follows the SPIRIT (Standard Protocol Items: Recommendation for Interventional Trials) 2013 Statement for trial protocols [24].

### Sample Size

There are very few studies that have examined the effects of digital solutions for personalized support and follow-up for patients undergoing day surgery. We based our sample size calculations on Jaensson et al [25], assuming that a better postoperative recovery (ie, decreased symptoms and complications) should reduce the number of postoperative calls to the health information line, visits to the emergency department, unplanned readmissions and medical visits, and the associated costs (our primary outcome). Jaensson et al [25] reported better recovery (based on the global Swedish Web Version of the Quality of Recovery [SwQoR] score) in an intervention group (ie, day surgery patients using a recovery assessment mobile phone app) compared with a control group (standard care) on POD 7 (effect size 0.21; *P*<.001). With a significance level of .05 and a statistical power of .90, G*Power (Heinrich Heine University) generated a group size of 357. To allow for a 20% rate of loss to follow-up and protocol deviations, we thus aim to recruit 500 patients per arm. In the third quarter of 2019, CHUM provided nearly 630 outpatient surgical stays per month on average. Considering 70% of patients should be eligible for the study [26], it will take about 12 months to recruit 1000 patients.

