**Methods:**

This study is a single-center, single-blinded, 2-group randomized controlled trial. One thousand patients aged over 18 years with internet access who are scheduled to undergo ambulatory surgery will be enrolled and randomized either to follow a perioperative path that includes a patient-tailored perioperative digital app via the LeoMed telecare platform for 1 month or to follow the standard of care, which does not offer personalized digital support. The primary outcome will be to evaluate the cost-effectiveness of the telecare platform, assessing direct costs from factors such as unanticipated cancellations on the day of surgery due to preoperative instructions not being followed, calls to the local health information line, calls to the provincial health information line, emergency department consultations, unplanned readmissions, or medical visits for problems related to the surgical procedure within the first 30 days after the intervention. The secondary outcome will be to evaluate cost utility using a questionnaire assessing quality-adjusted life years. A blinded independent research team will analyze outcomes. All data will be analyzed according to the intention-to-treat principle. A sample size of 500 subjects in each group was calculated to detect a 21% reduction in postoperative complications with a power of 90%. This study has been approved by the ethics board of Centre hospitalier de l’Université de Montréal (University of Montreal Health Centre). No employee of LeoMed was involved in the study conception, and none will be involved in either data collection or analysis.

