### Blinding and Allocation Concealment

Eligible patients will first be approached by telephone by a member of the research team when the preoperative clinical appointment is booked. During the preoperative clinical assessment, patients will receive both oral and written information on the study by a research nurse not involved in patient care. Patients will be included in the trial only after a research nurse has obtained written informed consent.

All included patients will be electronically randomized into the intervention group or the control group. Randomization will be performed by one of the investigators using the MedSharing Randomizer for Clinical Trial web application. The 2 groups will be balanced at a 1:1 ratio. Patients who are recruited but do not receive surgery within the study time frame will be secondarily excluded.

The study will be single-blinded. Statisticians will assess the primary and secondary outcomes, blinded to the randomization group. However, due to the nature of the intervention, neither the patients nor the care providers will be blinded to the randomization.

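### The group size of 357 is the 80% power answer for an effect size of 0.21 (two-sided t test), not the 90% answer; at the planned 20% loss, power is about 84%

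*Protocol article*

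**What the plan says.** The Sample Size section of the protocol article borrows its effect from an earlier trial of a recovery app in day-surgery patients. That trial reported a better global SwQoR score on postoperative day 7, with "effect size 0.21". The calculation is then given in one sentence: "With a significance level of .05 and a statistical power of .90, G*Power (Heinrich Heine University) generated a group size of 357". The next step is "To allow for a 20% rate of loss to follow-up and protocol deviations, we thus aim to recruit 500 patients per arm".

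Allocation is equal: "The 2 groups will be balanced at a 1:1 ratio" (Blinding and Allocation Concealment). The Sample Size section names neither the test nor the number of tails. The only mention of tails is in Data Analysis, a "2-tailed *t* test (for continuous data"), and it applies to demographic comparisons.

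The Abstract (Methods) restates the calculation differently: "A sample size of 500 subjects in each group was calculated to detect a 21% reduction in postoperative complications with a power of 90" percent.

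**The concern.** The section gives every number needed to check it: effect size, significance level, power and resulting group size. The familiar two-group calculation with these inputs gives a figure about a third larger than the one printed, so either the power or the group size is misreported. This is the article's only power statement, and it appears in both the Abstract and the Methods. A reader would credit the design with a 10% type II error for the assumed effect, which it may not have once the plan's own losses are taken off.

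**Working it through.** **Inputs.** d = 0.21, read as a standardised mean difference (Sample Size); alpha = .05 (Sample Size); power .90 (Sample Size and Abstract); 1:1 allocation (Blinding and Allocation Concealment); 500 recruited per arm and 20% loss (Sample Size). Assumed: a two-sample t test, two-sided. One-sided results are shown as well.

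**Formula.** The normal approximation per group is n = 2(z_alpha + z_power)²/d². The exact figures use the noncentral t distribution, which is the usual two-group t test calculation.

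**Step 1: reproduce 357.** With d² = 0.0441:

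- 80% power, two-sided: 2(1.960 + 0.842)²/0.0441 gives 356; exact 356.9, so **357**.
- 90% power, two-sided: 2(1.960 + 1.282)²/0.0441 gives 477; exact 477.5, so **478**.
- 90% power, one-sided: 2(1.645 + 1.282)²/0.0441 gives 389; exact 389.06, so **390**.

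The printed figure matches two-sided 80% power exactly. The two-sided 90% figure is 478/357 = 1.34 times as large.

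**Step 2: could rounding or another reading explain it?**

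- If 0.21 was rounded from anything between 0.205 and 0.215, the two-sided 90% requirement runs from 502 down to 456, and the one-sided from 409 down to 372. Neither range contains 357.
- Two-sided 90% power with 357 per group would need d = 0.243.
- A one-sided Wilcoxon test with a logistic parent distribution gives about 355.
- A 21% relative reduction in a complication proportion gives 357 at 90% power only if the control rate is about 57.6%.

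The last two come close or match, but only with inputs that the article does not state.

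**Step 3: power at the sizes that matter (d = 0.21, alpha .05, exact t).**

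| Analysed per arm | Two-sided | One-sided |
|---|---|---|
| 357 | 80.0% | 87.7% |
| 400 (500 × 0.80) | 84.3% | 90.7% |
| 447 (357/0.80) | 88.0% | 93.2% |
| 478 | 90.0% | 94.5% |
| 500 | 91.3% | 95.3% |

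Two-sided, 90% power with 500 recruited tolerates a loss of 1 − 478/500 = 4.4%. With 400 analysed per arm, two-sided 90% power applies to d of about 0.23 (0.2295).

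**Step 4: the inflation.** 357/0.80 = 446.25, so 447; the cruder 357 × 1.2 gives 429. Going from 357 to 500 corresponds to a loss of 1 − 357/500 = 28.6%, not 20%.

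**The case against.** The strongest reply is that sidedness is not stated and the hypotheses in the Introduction are directional. If the calculation was one-sided at .05, 400 analysed per arm gives 90.7% power, and the target is met after the planned loss. This stands as a limit on the 84% figure, which must carry its two-sided label. It does not rescue the printed calculation: one-sided planning at 90% gives 390, and an exact match with the two-sided 80% answer is hard to put down to chance. A reader might infer that 90% is missed on every reading, or that nothing could yield 357 at 90%. The documents support neither, for the reasons in the one-sided column and in Step 2.

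A second reply is that recruiting 500 rather than 447 errs on the safe side. That is right. The excess raises two-sided power after 20% loss from the 80% that 357 would give to 84%. The mismatch matters only because the text presents 500 as following from 357 and 20%.

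A third concerns the attrition allowance. One might argue that protocol deviations have no place in it, because Data Analysis promises intention-to-treat. The documents do not support removing them. Population excludes randomised patients who convert to an inpatient stay or whose surgery is postponed at the last minute, and Blinding and Allocation Concealment excludes those not operated on within the study time frame. An allowance beyond loss to follow-up is therefore needed. How those exclusions fit with intention-to-treat is a separate matter.

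Finally, the effect is a day 7 recovery score that Table 1 does not list among the assessments, while the primary outcome is cost-effectiveness. It is tempting to say that a null primary result would carry a 16% type II error instead of 10%. The article gives no cost variance or target cost difference, so neither figure describes that outcome.

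**Conclusion.** The stated power does not match the stated inputs. Assuming a two-sided two-sample t test, 357 per group delivers 80% power for d = 0.21, and 90% needs 478 analysed per group. At the plan's own 20% loss the design has about 84% power, a type II error of about 16% (1 − 0.843) for the recovery-score effect. The Abstract's 90% for 500 per group is right only with nearly complete follow-up, and it attaches to an effect described differently from the one in the Sample Size section.

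The conclusion rests on reading 0.21 as a standardised mean difference and on two-sided testing. The mismatch between 357 and 90% also holds one-sided under a t test; the shortfall at 400 per arm does not. A reader might infer that the trial must be enlarged to 478/0.80 = 598 per arm. That does not follow: 84% is a defensible power if it is declared, and the figure concerns a surrogate for the primary outcome.

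**What to change.** Keep the total at 1000 and correct the text in two places.

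- **Sample Size:** name the test and its sidedness. If two-sided, say that 357 per group corresponds to 80% power, that 90% needs 478 analysed per group, and that 500 recruited less 20% leaves 400, with about 84% power for d = 0.21 (90% for d of about 0.23). Present 500 as chosen above the 447 that a 20% allowance would require. If a one-sided test was intended, say so and replace 357 by 390. Keep the attrition allowance. State that the power refers to the recovery score and not to the cost-effectiveness outcome.
- **Abstract, Methods:** correct the power in the same way, and describe the effect as a standardised effect size of 0.21 on a recovery score, not as a percentage reduction in complications.

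The cost is wording only: no extra patients and no change to design or analysis. Under the two-sided reading the declared power falls from 90% to about 84%. With 142 patients enrolled by October 31, 2022 (Results), the correction can be on record well before the analysis.

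### The 20% allowance pools loss to follow-up with protocol deviations at an undiluted effect of 0.21, which does not fit intention-to-treat; 500 per arm then gives at most about 84% to 85% two-sided power, not 90%

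*Protocol article*

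**What the plan says.** All references are to the protocol article; no separate analysis plan is at hand.

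- **Sample Size.** The effect comes from a published trial of a recovery app in day surgery, on a recovery score at postoperative day 7 ("effect size 0.21; *P*<.001"). Then: "With a significance level of .05 and a statistical power of .90, G*Power (Heinrich Heine University) generated a group size of 357". Then: "To allow for a 20% rate of loss to follow-up and protocol deviations, we thus aim to recruit 500 patients per arm". The 20% is not split, a deviation is not defined, and 0.21 is not reduced.
- **Data Analysis**, repeated in the Abstract: "All data will be analyzed according to the intention-to-treat principle".
- **Abstract, Methods.** The 90% is attached to the enrolled number: "A sample size of 500 subjects in each group was calculated to detect a 21% reduction in postoperative complications with a power of 90"%.
- **Population** and **Blinding and Allocation Concealment.** Some randomised patients are excluded afterwards: those converted to inpatient stay on the day of surgery, those whose surgery is postponed at the last minute, and those not operated on within the study period. Allocation is 1:1.

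**The concern.** Enrolling extra patients at an unchanged effect size replaces observations that will be missing from the analysis. That is the right correction for patients with no outcome. It is the wrong one for patients who deviate but whose outcome is known. Under intention-to-treat they still count in their arm, so the analysed number does not fall. What may fall is the average effect.

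This intervention leaves room for such patients. It depends on opening notifications and completing forms on the first four days after surgery (Intervention Group). Outcome loss is limited by telephone follow-up at day 30 and a cross-check with the medical record (Data Collection). Part of the 20% could therefore be non-use rather than missing data, although the article does not say so.

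At stake are the power that the trial can claim and the clarity of the analysis set. Two parts of the article currently imply different treatment of the same patients.

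**Working it through.** **Inputs.** Effect 0.21, read as a standardised mean difference; alpha .05; power .90; 357 per group; 20% allowance; 500 per arm (all Sample Size). Ratio 1:1 (Blinding and Allocation Concealment). Sidedness is not stated for the sizing; two-sided is used, and one-sided is shown where it matters.

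**Step 1: the plan's own figures.** Two-sample t test (noncentral t), effect 0.21:

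- 90% power, two-sided: 477.5, so 478 per group. One-sided: 389.1, so 390.
- 80% power, two-sided: 356.9, so 357.
- Power at 357: 80.0% two-sided, 87.7% one-sided.

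The stated 357 is thus the two-sided number for 80% power. It does not give 90% on either sidedness.

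The allowance does not reproduce either: 357/(1 − 0.20) = 446.25, so 447, not 500. The step from 357 to 500 corresponds to 1 − 357/500 = 28.6% attrition. For a true 90% with 20% lost, 478/0.80 = 597.5, so 598 per arm.

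**Step 2: 500 per arm, all 20% leave the analysis.** 500 × 0.80 = 400 per arm, effect 0.21: power 84.3%. Shortfall against 90%: 90 − 84.3 = 5.7 points, with no dilution involved. With nobody lost and nobody deviating, 500 per arm gives 91.3%.

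**Step 3: deviators stay in.** Let L be the share lost and D the share deviating, with L + D = 0.20. Let k be the share of the benefit that a deviator loses. Then

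- analysed per arm: n = 500 × (1 − L)
- average effect: 0.21 × [1 − k × D/(1 − L)]

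Assumptions: equal loss in both arms, unchanged standard deviation, and an effect altered only by deviators in the intervention arm. The split and k are not in the article, so a range is shown (two-sided).

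| L | D | n per arm | Effect, k = 1 | Power, k = 1 | Power, k = 0.5 |
|---|---|---|---|---|---|
| 20% | 0% | 400 | 0.210 | 84.3% | 84.3% |
| 15% | 5% | 425 | 0.198 | 82.1% | 84.3% |
| 10% | 10% | 450 | 0.187 | 79.9% | 84.4% |
| 5% | 15% | 475 | 0.177 | 77.7% | 84.6% |
| 0% | 20% | 500 | 0.168 | 75.6% | 84.7% |

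For example, at L = D = 10% and k = 1: n = 500 × 0.90 = 450, and the effect is 0.21 × (1 − 0.10/0.90) = 0.187.

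The cost of dilution against removal is at most 84.3 − 75.6 = 8.7 points (k = 1, all deviators). At k = 0.5 it is nil, because the retained patients offset the smaller effect.

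**Step 4: if the 20% is reserved for missing outcomes and non-use comes on top.** 400 analysed per arm:

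- effect reduced by a tenth, 0.21 × 0.9 = 0.189: power 76.1%
- effect reduced by a fifth, 0.21 × 0.8 = 0.168: power 66.0%

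These are lower than in the table because loss and deviation no longer share one 20%.

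**The case against.** The article never says that deviators are removed, never defines a deviation and never calls non-use one. The only departures after randomisation that it names are conversion, postponement and no surgery within the period, and those patients are excluded. If they are what the allowance means, adding patients is the right correction and nothing is diluted. The 0.21 may also come from a comparison that already included non-users. And all these figures are for a recovery score used as a proxy, not for the cost-effectiveness outcome.

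Most of this stands, and it limits the point. A reader might infer that the trial is sized for a per-protocol analysis, or that analysts are being invited to drop non-users. The documents do not support that: removal is only implied by the arithmetic, intention-to-treat is stated for all data, and the statisticians are blinded to group. A reader might also put the whole gap below 90% down to deviations. That is not supported either, since 5.7 points of it exist with no deviators at all.

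The objection does not remove the ambiguity. If the deviations are the excluded patients, the unqualified intention-to-treat statement needs qualifying. If they are patients who stay in, the allowance uses the wrong correction. Nor does it rescue the 90%: on a two-sided test, removing the full 20% gives 84.3%.

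One-sided testing would give 90.7% at 400 per arm. The article does not state a one-sided test, and 357 matches the two-sided number at 80% power.

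**Conclusion.** The point holds in a limited form. The pooled allowance fits the stated intention-to-treat analysis only for patients who leave the analysis, and the article does not say who they are. With a two-sided test, an effect of 0.21 and the article's own 20%, 500 per arm gives about 84% to 85% power at best and 75.6% at worst over the range examined. The 90% is not delivered.

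The two parts of the shortfall differ in certainty. The 5.7 points before dilution follow from the stated inputs, given a two-sided test. The further 0 to 9 points are conditional. The upper end needs all 20% to be deviators with no benefit and nobody lost, and the cost is nil if deviators keep half the benefit. If 0.21 already includes non-users, part of the dilution is already counted. That deviations lower power is therefore possible but not established, and its size cannot be fixed from this document.

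**What to change.** In the Sample Size section:

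1. Restrict the 20% allowance to patients without an outcome and take protocol deviations out of it.
2. State that non-users and other deviators are analysed in the arm to which they were randomised. Reconcile this with the exclusions in Population and in Blinding and Allocation Concealment, so that the article says which randomised patients are left out and whether the allowance covers them.
3. State the sidedness, and replace the 90% here and in the Abstract with the power at 500 per arm. Two-sided, that is at most about 84% with 20% missing. It is lower under a stated non-use assumption, for example 76% if the effect is reduced by a tenth. Say whether 0.21 already reflects non-use.

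The cost is wording and a less favourable stated power. No extra patients or data are needed.
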